**DASH disorder/symptom score=[Sum of score filled item]/n-1]25**

* n refers to the number of question filled by the subject and the DASH disorder/symptom score can’t be calculated when more than 3 items weren’t filled.

The calculated scores will be used to analyze the significance comparatively by performing the one side and two sample student T-test with the variances of between two groups measured at each period (from preoperative day to 3, 6, and 12 months following the surgery).

- The evaluation on pain derived from the movement

The subject selects the pain level within the diagram designed using VAS (visual analogue scale is the verified assessment tool., 0 means the absence of pain and 100 means the worst pain) stated in the questionnaire, and the examiner measures the distance between the starting point and the ending point after measuring it using the ruler. The calculated values will be used to analyze the significance comparatively by performing the one side and two sample student T-test with the variances of between two groups measured at each period (from preoperative day to 3, 6, and 12 months following the surgery).

**15-2 Safety Criteria Analysis**

(1) Adverse Events

All the AE that developed during the study period were analyzed. Their onset rate, the onset rate of AE that caused dropout, and the onset rate of SAE were summarized by group. They were coded using WHO-ART, then tested through the Chi-square test or Fisher’s exact test. The onset rates of AE were suggested as: onset rate of all adverse events, and the onset rate associated with the investigational device.

(2) Laboratory Tests

In the case of baseline continuous data from the laboratory test, descriptive statistics quantity (such as mean, SD, median, minimum, and maximum) was calculated, and their normal distribution was tested, then the difference between the groups was compared using One side, Two sample student t-test. In the case of categorical data, their descriptive statistics quantity (frequency and percentage) was suggested, and the difference between the groups was compared using the Chi-square test or Fisher’s exact test. After checking the investigational group’s test value came out on preoperative day and the 7th day following the surgery is different from it of control, we checked whether this difference is included within the normal error range or not.

1) Assessment of Criteria: Adverse events (Visit2, Visit3, Visit4, Visit5) and Hematologic Tests (Visit1, Visit2)

2) Evaluation criteria: The safety of investigational device is considered to be confirmed if the difference between the investigational group’s result value and control’s result value isn’t significant.

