Methods of preventing adhesion may include the minimization of surgical wounds, use of anti-inflammatory agents, and activation of tissue plasminogen activators for inhibiting fibrin formation [18]. Recently physical barriers have also been developed and used [19]. Barriers function as a physical barrier during the tissue healing period and prevent adhesion formation around the tissues. Upon completion of wound healing, the barrier must be dissolved or absorbed to be removed. The barrier itself and its dissolved ingredients must be harmless to the body. Adhesion prevention materials may include oxidized regenerated cellulose, sodium carboxymethyl cellulose (CMC), dextran, and sodium hyaluronate (HA), which are made from nature-derived polysaccharides. Synthetic polymers may include polyethylene glycol (PEG), poloxamer, and Gore-Tex.

The anti-adhesive agent, which builds the physical barrier, is made from the various materials and its type is various. The double liquid type has a convenient usage of which solution is applied underneath the wound directly and used well since it can be used in the laparoscopic surgery. However, it has a weakness of which efficacy is reduced when its liquid solution flows.

GUARDIX SG is prepared using poloxamer, a synthetic macromolecule, and alginate, a natural macromolecule. It is liquid at room temperature, but when applied to surgical sites, it reacts to the body temperature to function as a gel. As a temperature-sensitive adhesion barrier, it remains in the body for up to 7 days according to in vivo experiments, then begins to dissolve after the 14th day and then is completely dissolved by the 21st day [20].

Guardix SG is the efficacy of anti-adhesive agent is already confirmed at the rat and the anti-adhesive efficacy and safety of it is confirmed clinically by using it for the patient who underwent spondylectomy and the thyroidectomy [18-20, 22].

Based on the above-mentioned grounds, we intended to evaluate the safety of Guardix SG and the preventive efficacy of Guardix SG for the dysfunction of upper limbs within the breast cancer patients who underwent the modified radical mastectomy or the breast preservation surgery along with the modified axillary lymph node dissection for 12 months by conducting observation study following the surgery.

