**12-4 Expected adverse events when using the anti-adhesive agent**

Infection: Fever and increase in WBC, Allergic reactions: Systemic rash, dyspnea, and edema, Pain, Inflammation

* Guardix SG (Anti-adhesion) is to prevent the adhesion having a physical barrier in order for the fibroid tissue to infiltrate to the damaged tissue. We recorded the degree of adverse events ranging from mild, moderate, and severe depending on the patient and the state since its degree is diverse regardless of same symptom.

(1) Mild: The degree of adverse events is mild.

(2) Moderate: The degree of adverse events is moderate.

(3) Severe: The degree of adverse events is severe.

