**14-3. Assessment of Other Criteria**

The postoperative drainage volume, postoperative therapy (cancer chemotherapy, anti-hormone therapy, target therapy, radiotherapy)

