**16-2 Adverse Events Definitions**

(1) Adverse Events, AE

AE is all the unintended syndromes (including signs and lab test results), symptoms, or diseases, which develop in the subjects during the clinical trial period. They are not necessarily associated with the investigational device. Expected daily fluctuations in the test disease or previous clinical manifestations, which are not clinically significant, are not required to be reported.

All AE that developed since the beginning of the clinical trial must be reported. The time of starting the clinical trial is the time of receiving the signed written consent. (Written consent must be obtained before special diagnoses or treatment is started.) All the AEs that developed after the written consent was received must be reported regardless of the administration or association with the investigational device.

(2) Adverse Device Effects, ADE

ADE is the hazardous and unintended reactions caused by the investigational device, whose causal relationship with the investigational device cannot be denied.

(3) Serious AEs · ADEs

One of the following AE or ADE that developed during the clinical trial period due to the investigational device.

1) Death or life-threatening danger

2) Hospitalization or extension of hospitalization

3) Permanent or serious impairment, or deteriorated functions

4) Fetal deformity or anomaly

(4) Unexpected Adverse Device Effects, UADEs

Not considered as significant ADE patterns and hazards according to the information related to the investigational device, as specified in the Investigator’s brochure or attached documents.

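### Safety is judged on all-cause adverse event rates over 12 months with no early-onset comparison, so background events in both arms dilute any early device-related excess

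*Protocol*

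**What the plan says.** **Scope of events.** Section 15-2 (1), and 16-1 (1) in the same words, sets the scope: "All the AE that developed during the study period were analyzed". The assessment list in 15-2 places adverse events at Visits 2 to 5, that is, to month 12. Section 16-2 (1) makes reporting independent of cause: "All the AEs that developed after the written consent was received must be reported regardless of the administration or association with the investigational device".

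**Rates and tests.** Sections 15-2 (1) and 16-1 (1) summarise all adverse events, those causing dropout and serious ones by group. They present the "onset rate of all adverse events, and the onset rate associated with the investigational device". On testing: "They were coded using WHO-ART, then tested through the Chi-square test or Fisher’s exact test".

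**Decision rule.** Section 15-2, evaluation criterion 2): "The safety of investigational device is considered to be confirmed if the difference between" the two groups' results is not significant. No margin is given.

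**Device residence.** Section 6-2, citing in vivo experiments, says the material stays for up to 7 days, "then begins to dissolve after the 14th day and then is completely dissolved by the 21st day".

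**Concurrent treatment.** Section 14-3 lists "postoperative therapy (cancer chemotherapy, anti-hormone therapy, target therapy, radiotherapy") among the other criteria, and 11-1 (4) and the Visit 2 list in 11-4 also record it.

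**Expected device events.** Section 12-4: "Infection: Fever and increase in WBC, Allergic reactions: Systemic rash, dyspnea, and edema, Pain, Inflammation".

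**Timing data.** Section 16-3 has the onset date of each event entered in the CRF.

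**The concern.** The device is a single intraoperative application with a described residence of about three weeks, while the compared rate accumulates events for a year. Many of those events may come from cancer treatment given equally to both arms. The events expected from the device (fever, rash, dyspnea, edema, pain, inflammation) are non-specific, so a coded term without an onset window does not show whether the event arose while the device was present.

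A subject who has an early event and a subject who has only a late one count the same in an any-event rate. As late events become more common, an early excess becomes a smaller difference on a higher base. In an efficacy comparison, dilution works against the sponsor's claim. Here the rule reads non-significance as safety, so dilution works in favour of the claim. What is at stake is the trial's safety conclusion, and 6-2 names the evaluation of safety as an aim.

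**Working it through.** **The plan's own figure.** The protocol gives no power or sample size for safety. Its efficacy size reproduces: margin 10, true difference 15, SD 10 and one-sided 0.025 give t-test power 0.903 at 86 per arm, and 86 / 0.90 = 95.6, rounded up to 96. I use 96 per arm, the most favourable case for the safety comparison.

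**Inputs from the protocol.** 96 per arm (8-3); chi-square or Fisher test (15-2); all-cause events to month 12 (15-2, 16-2); dissolution by day 21 (6-2).

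**Assumptions, because the protocol gives no figure.**
- Two-sided 5% level; 15-2 states no level for the adverse event tests.
- An early event, during the device period, in proportion e (device) and c (control).
- A later background event in the same proportion b of both arms, independent of the early one. b is varied from 0 to 0.9.

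**Formulas.** Any-event rate in the device arm = 1 − (1 − e)(1 − b); in the control arm = 1 − (1 − c)(1 − b). The difference is (e − c)(1 − b), so background shrinks the early excess by the factor 1 − b. Power is by exact binomial enumeration over all outcomes with 96 per arm.

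**Main case, e = 15%, c = 5%.**

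| b | Device | Control | Difference (points) | Chi-square power | Fisher power |
|---|---|---|---|---|---|
| 0 (early window only) | 15.0% | 5.0% | 10 | 66% | 56% |
| 0.3 | 40.5% | 33.5% | 7 | 17% | 13% |
| 0.5 | 57.5% | 52.5% | 5 | 11% | 8% |
| 0.7 | 74.5% | 71.5% | 3 | 8% | 6% |
| 0.9 | 91.5% | 90.5% | 1 | 6% | 3% |

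Example for b = 0.5: 1 − 0.5 × 0.85 = 0.575 and 1 − 0.5 × 0.95 = 0.525.

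**Other early rates (chi-square).** For 20% v 5%, power falls from 91% to 32% at b = 0.3 and 11% at b = 0.7. For 25% v 10%, it falls from 80% to 31% and 11%. The loss is already large at 30% background, so it does not depend on rates near a ceiling.

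**Do the other planned summaries isolate the early period?**
- *Device-associated rate.* The first causality item in 16-4-1 asks whether the subject was exposed to the device. Controls receive nothing (10.2), so they cannot meet it, and the rate is not a like-for-like comparison.
- *WHO-ART terms.* These narrow the type of event but not its timing.
- *Visit listing.* Visits go from day 7 to month 3, so no visit boundary falls near day 21.
- *Serious events and events causing dropout.* These would miss ordinary infectious, allergic or local events.

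**The case against.** **The all-event rate is not the only one planned.** True. Sections 15-2 and 16-1 also give device-associated, serious and dropout-causing events, and coding allows tests by term. The causality grades in 16-4-1 weigh time course and alternative causes. Visit 2 captures events to day 7, when the material is still described as present. This stands as partial protection, within the limits shown in the working.

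**The size is assumed.** Also true. Neither the early nor the background rates are in the protocol, and section 8-1 admits patients who had preoperative chemotherapy, so the share treated after surgery is unknown. A reader might infer that cancer-therapy toxicity swamps the comparison, so that safety would be declared almost regardless of what the device did. The documents do not support that. They give no rates that put the comparison near its ceiling, and randomisation makes the background equal in expectation. The effect is dilution, not bias.

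**Late events can matter.** This stands. The day-21 figure comes from in vivo experiments whose cited source is titled as a rat model. The trial itself expects an early barrier to affect outcomes up to 12 months, so harm may also appear late. Collecting and comparing events over 12 months is not an error, and moving them to a purely descriptive table would be hard to defend.

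**An onset window is SAP detail.** An extra table could be left to the SAP. But this protocol itself fixes the event scope, the tests and the rule for declaring safety, so the combination can be criticised here.

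**The deeper fault is the non-significance rule.** This stands too. With the early window alone, a 15% v 5% harm would still be missed in about 34% of trials by chi-square (1 − 0.66) and 44% by Fisher (1 − 0.56).

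**Conclusion.** The point holds as one of dilution. The protocol compares all-cause adverse events over 12 months, sets no between-arm comparison for the period when the device is described as present, and takes non-significance as confirming safety. Under the assumed 15% v 5% early rates, chi-square power of about 66% falls to 17% at 30% background and 6% at 90%. The absolute figures depend on the assumed rates, the independence of early and late events, and a two-sided 5% level. The shrinkage of the difference by the factor 1 − b holds for any early rates under the equal and independent background assumed here.

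Two further inferences are not supported: that 12-month collection is itself wrong, and that an early window alone would make the safety conclusion sound. The first ignores delayed harm; the second leaves the non-significance rule in place.

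**What to change.** In 15-2 (1) and 16-1 (1):

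- Keep the 12-month comparison of all adverse events and serious adverse events.
- Add a pre-set between-arm comparison of subjects with at least one adverse event, and at least one serious adverse event, with onset from surgery to about day 30. Include the expected infectious, allergic and local events. About day 30 covers the described 21-day residence with some allowance; the protocol gives no start date for adjuvant therapy, so the window reduces background and may not remove it.
- Report risk differences with confidence intervals for both windows, using the recorded onset dates.

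In 15-2, evaluation criterion 2), base the safety conclusion on both windows and their confidence intervals, not on non-significance of the 12-month rate.

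Cost: wording in two sections and one more table, with no new visit or data item. The weak spot is that onset dates between day 7 and month 3 rest on what is recorded at Visit 3.

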**H_0_ : D ≤ 10 H_1_ : D〉10 (D=Experimental group(EG) ROM Mean – Control group(CG) ROM Mean)**

* Basis of Calculation: Assumptions for estimating the effective subject number.

① Significance level α = 0.025

② The EG estimation number is 1 time that of CG.

③ Type 2 error (β) is 0.1, and statistical power 90% is maintained.

④ The difference in the average value between two groups: 10 degree.

[figure not shown]

[figure not shown]

[figure not shown]

| Power | N1/N2 | Equivalence Margin  (E) | Actual  Difference  (D) | Significance  Level  (Alpha) | Beta | Standard  Deviation1  (SD1) | Standard  Deviation2  (SD2) |
| --- | --- | --- | --- | --- | --- | --- | --- |
| 0.90022 | 23/23 | 5 | 10 | 0.025 | 0.09978 | 5 | 5 |
| 0.80044 | 17/17 | 5 | 10 | 0.025 | 0.19956 | 5 | 5 |
| 0.90004 | 86/86 | 5 | 10 | 0.025 | 0.09996 | 10 | 10 |
| 0.80003 | 64/64 | 5 | 10 | 0.025 | 0.19997 | 10 | 10 |
| 0.90022 | 191/191 | 5 | 10 | 0.025 | 0.09978 | 15 | 15 |
| 0.80044 | 143/143 | 5 | 10 | 0.025 | 0.19956 | 15 | 15 |
| 0.91250 | 23/23 | 10 | 15 | 0.025 | 0.08750 | 5 | 5 |
| 0.80704 | 17/17 | 10 | 15 | 0.025 | 0.19296 | 5 | 5 |
| 0.90323 | 86/86 | 10 | 15 | 0.025 | 0.09677 | 10 | 10 |
| 0.80146 | 64/64 | 10 | 15 | 0.025 | 0.19854 | 10 | 10 |
| 0.90022 | 191/191 | 10 | 15 | 0.025 | 0.09978 | 15 | 15 |
| 0.80044 | 143/143 | 10 | 15 | 0.025 | 0.19956 | 15 | 15 |

Suppose that the 10% subject is dropped out in the middle of trial, the necessary total subject is 192 persons composing of 96 persons for the experimental group and 96 persons for the control.

| Target subject number | EG | CG | In total subject number |
| --- | --- | --- | --- |
| Subject number for final efficacy evaluation | 86 | 86 | 172 |
| Subject number in consideration of drop-out rate (10%) | 96 | 96 | 192 |

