**10.2 Comparator device**

The Comparator device referred as an inactive control isn’t used in this clinical trial.

[Currently, it is uncommon to apply the anti-adhesive agent onto the surgical site of patient who underwent the modified radical mastectomy or breast preservation surgery and the axillary lymph node dissection and it is safe to apply nothing to the surgical site. Therefore, we couldn’t find the reference medical device and didn’t assigned any medical device as the control.]

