**16. Assessment of Safety Criteria, and Evaluation and Side Effect Report (including adverse events)**

**16-1 Assessment of Safety Methods**

The adverse events confirmed at the physico-chemical exam or reported from the subject are included in the analysis for evaluating the occurrence rate of adverse events which occurred within the investigational group and control and its severity and its type.

(1) Adverse events

All the AE that developed during the study period were analyzed. Their onset rate, the onset rate of AE that caused dropout, and the onset rate of SAE were summarized by group. They were coded using WHO-ART, then tested through the Chi-square test or Fisher’s exact test. The onset rates of AE were suggested as: onset rate of all adverse events, and the onset rate associated with the investigational device.

(2) Laboratory Tests

In the case of baseline continuous data from the laboratory test, descriptive statistics quantity (such as mean, SD, median, minimum, and maximum) was calculated, and their normal distribution was tested, then the difference between the groups was compared using the independent t-test or Wilcoxon’s rank sum test. In the case of categorical data, their descriptive statistics quantity (frequency and percentage) was suggested, and the difference between the groups was compared using the Chi-square test or Fisher’s exact test.

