**16-4-1. Causal Relationship Between AE and the Investigational Device**

Evaluation of the causal relationship is very important to determine the prompt report. The following items are considered for the causal relationship evaluation.

(1) Exposure: Was the subject exposed to the investigational device?

(2) Time course: Did AE develop according to the time course after applying the investigational device?

(3) Likely: Is the AE development explained better with the application of the investigational device than with baseline diseases or other factors?

(4) Dechallenge: Was the AE relieved or disappeared by discontinuing the use of investigational device?

(5) Rechallenge: Was the AE relieved or disappeared by reapplying the device?

Methods of classifying the evaluation results of the causal relationship with AE (by the WHO).

| Classification | Evaluation Results |
| --- | --- |
| Definitely | Valid time course is shown with the application of the investigational device.  Cannot be explained with diseases or other causes.  When discontinued, symptoms react.  When rechallenged, symptoms react. |
| Probable | Valid time course is shown with the application of the investigational device.  Difficult to explain with diseases or other causes.  When dechallenged, symptoms react.  Rechallenge is not required |
| Possible | Valid time course is shown with the application of the investigational device.  Can be explained with diseases or other causes.  When dechallenged, reactions can be mild or unclear. |
| Unlikely | Valid time course may be minimal with the application of the investigational device.  Can be explained with diseases or other causes.  When dechallenged, reactions can be mild or unclear. |
| Unrelated | No time course with the application of the investigational device.  Clearly explained with diseases or other causes.  When dechallenged, no reactions. |
| Unclassified | Unable to evaluate due to insufficient or contradictory information.  Data cannot be supplemented or confirmed. |

The causal relationship between AE and investigational device (or other causes such as baseline disease and combined treatment) is determined based on the following factors:

◆ Known functions of the investigational device

◆ Functions previously observed in the investigational device or the same series device as the investigational device

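### The protocol lets a device-associated adverse event rate, which has no valid counterpart in an untreated control arm, enter the by-group safety test and the safety conclusion

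*Protocol*

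**What the plan says.** Section 15-2(1) summarises by group the rates of adverse events, of events leading to dropout and of serious events. Section 16-1(1) repeats that text. Both then state the test: "They were coded using WHO-ART, then tested through the Chi-square test or Fisher’s exact test". The next sentence names the rates to be shown: "The onset rates of AE were suggested as: onset rate of all adverse events, and the onset rate associated with the investigational device".

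Section 15-2 lists adverse events (Visits 2 to 5) among its safety assessments and closes with a decision rule: "The safety of investigational device is considered to be confirmed if the difference between the investigational group’s result value and control’s result value isn’t significant". The rule does not say whether the all-event rate, the device-associated rate or both are meant.

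On the control arm, section 10.2 says: "The Comparator device referred as an inactive control isn’t used in this clinical trial".

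Section 16-4-1 lists the items to weigh for causality, and the first is "Exposure: Was the subject exposed to the investigational device". In its table, the grades Definitely, Probable and Possible each require a valid time course relative to application of the device. Possible also admits events that other causes could explain.

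Section 16-3 gives adverse event evaluation to the principal investigator or investigators and does not say whether they are blinded. The title in section 1 and the design text in 10.3 describe blinded assessment.

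**The concern.** A between-arm comparison can be interpreted only if the outcome is ascertained by the same rule in both arms. The all-event rate meets that condition. The device-associated rate does not, because its definition depends on having received the device.

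The device arm can collect related labels without any excess harm. Infection and pain are listed both as expected device events (12-4) and as expected surgical events (12-5). A postoperative infection can be graded Possible after Guardix SG, while the same infection in a control does not meet that grade as written.

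At stake is the safety conclusion. Under the 15-2 rule a significant group difference means safety is not confirmed. If the rule takes in the device-associated rate, the device could fail with identical all-cause event rates in the two arms. Such a result would reflect labelling practice rather than harm.

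**Working it through.** **1. Group size.** Section 8-3 sizes the trial for efficacy with "Significance level α = 0.025" and "Type 2 error (β) is 0.1, and statistical power 90% is maintained". The row it uses has margin 5, difference 10 and SD 10. With an effective difference of 10 − 5 = 5, the normal approximation gives 85 per arm. The noncentral t gives 86 (power 0.8999 at 85 and 0.903 at 86). Allowing for 10% dropout, 86 / 0.9 = 95.6, so 96 per arm. The protocol's 86 and 96 are reproduced. No sizing, event rate or test level is given for adverse events.

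**2. Can a control event be device-associated under 16-4-1?**
- *Grader knows the allocation.* Nothing was applied, so no time course from application exists. Definitely, Probable and Possible are all unavailable, and the control count is structurally zero.
- *Grader is blinded.* The exposure item cannot be answered, nor can a time course from application be established. A control event might still be labelled related, but not by following the section as written.

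**3. Significance threshold with no control cases.** For k of 96 against 0 of 96, the one-sided Fisher p-value is C(96,k) / C(192,k). With equal arms the two-sided value is twice that. For k = 6:

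(96/192)(95/191)(94/190)(93/189)(92/188)(91/187) = 0.0144; doubled, 0.0288.

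| k in device arm | Fisher, two-sided | Chi-square, uncorrected |
|---|---|---|
| 4 | 0.121 | 0.043 |
| 5 | 0.059 | 0.023 |
| 6 | 0.029 | 0.013 |
| 7 | 0.014 | 0.007 |

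At an assumed two-sided 5% level, Fisher is significant from 6 patients (6/96 = 6.3%) and uncorrected chi-square from 4. A one-sided 0.025 level gives the same Fisher threshold (0.0296 at k = 5, 0.0144 at k = 6). With 86 per arm the Fisher threshold is again 6 (p = 0.029).

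**4. Chance of a false excess.** Let r be the share of device-arm patients with an event labelled related, with all-cause rates equal in the two arms. The chance is P(X ≥ 6) for X ~ Binomial(N, r). The values of r are assumptions.

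| r | Fisher, N = 96 | Fisher, N = 86 |
|---|---|---|
| 2% | 1% | 0.8% |
| 3% | 7% | 4% |
| 5% | 35% | 26% |
| 8% | 79% | 69% |
| 10% | 93% | 87% |

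Uncorrected chi-square (threshold 4, N = 96) gives 13%, 33%, 71%, 95% and 99%.

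**5. Benchmark.** Comparing all events whatever their attribution, with equal true rates of 5% to 30% and 96 per arm, Fisher gives a false-positive rate of about 2% to 3.5%.

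**The case against.** Four points can be made against this.

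*No test of this rate is stated.* The test sentence comes before the sentence that names the device-associated rate and refers back to the rates already summarised. The later sentence can be read as descriptive reporting only. This stands in part: a reader might infer that the protocol expressly orders the test, and it does not. But the two sentences are consecutive within one by-group analysis, and nothing excludes the test.

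*The control rate need not be zero.* The tempting stronger reading is that every control event must be graded Unrelated. The documents do not support that unconditionally. The trial is described as assessor-blinded, exposure is one of five items to consider, no rule maps non-exposure to Unrelated, and an Unclassified grade exists. The structural zero holds if the grader knows the allocation. Blinding does not rescue the comparison, though, because 16-4-1 cannot then be applied as written, and 16-3 does not say the graders are blinded.

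*The safety rule may not use this rate.* It names neither rate, so a reader should not infer that the device will be judged on the device-associated one. The ambiguity is itself the defect.

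*The effect may be small.* If few events are labelled related, it is: about 1% at a 2% share. Events expected from surgery may well be graded Unlikely or Unrelated. The high figures are illustrations, not forecasts.

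A statistical analysis plan could settle which tables carry p-values. The protocol, however, already fixes the rates, the tests, the causality scheme and the decision rule, and it is their combination that fails.

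**Conclusion.** The point holds in limited form. As written, the protocol permits an uninterpretable by-arm comparison of device-associated events to enter the safety conclusion. It does not explicitly require that comparison, and the all-event comparison is sound.

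If the rate is tested with no related events in controls, six labelled patients among 96 suffice by Fisher's test. The chance of a false excess then runs from about 1% to 93% as the labelled share goes from 2% to 10%. This rests on three assumptions: the share labelled related, a two-sided 5% level, and a control count of zero. The protocol gives no figure for the first two, and the third depends on allocation-aware grading. The primary efficacy analysis is not touched. The wording should be corrected.

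**What to change.** In 15-2(1), 16-1(1) and the 15-2 evaluation criterion, state that the between-arm comparison and the safety conclusion use all-cause events only: any adverse event, serious events, events causing dropout, and the expected events of 12-4 and 12-5 by type. Give the risk difference with a 95% confidence interval for each.

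Report device-associated events as a count and percentage in the Guardix SG arm, with no between-arm test and no role in the criterion. State in 16-3 whether those who grade causality are blinded, and reconcile this with the exposure item in 16-4-1.

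The cost is a wording amendment. It needs no new data, visits or patients, and the only thing lost is a comparison that cannot be interpreted.

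### Sections 15-2 and 16-1 name different tests for the same laboratory safety comparison, and the one-sided version in 15-2 has no stated direction and cannot register a difference in the opposite tail

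*Protocol*

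**What the plan says.** Section 15-2 (2), Laboratory Tests, opens "In the case of baseline continuous data from the laboratory test", lists descriptive statistics, adds "and their normal distribution was tested", and ends: "the difference between the groups was compared using One side, Two sample student t-test". It names no alternative if normality fails, no direction for the one-sided test and no significance level. A later sentence turns to preoperative and day-7 values and asks whether the difference between arms lies within normal error; it names no test.

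Section 16-1 (2) has the same opening, the same descriptive statistics and the same normality check, but ends: "the difference between the groups was compared using the independent t-test or Wilcoxon’s rank sum test". Sidedness is not stated.

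Section 15-3 (1) lists the methods as the one-sided two-sample t-test, chi-square and Fisher's exact test.

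The safety criteria in 15-2 are adverse events and haematology at Visits 1 and 2, with this rule: "The safety of investigational device is considered to be confirmed if the difference between the investigational group’s result value and control’s result value isn’t significant".

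The only alpha in the protocol is 0.025, given for the sample size in section 8-3. Footnote 2 to the Clinical Trial Schedule (repeated in 11-4) restricts the day-7 blood test to subjects with signs such as flare at the surgical site or fever.

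**The concern.** The same comparison is specified twice, differently, and the result feeds a conclusion about safety. This is not detail left open for an SAP: the protocol fixes the test in both places.

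Section 15-2 also has two faults of its own. First, its normality check has no consequence, because a Student t-test follows whatever the check shows; in 16-1 the same check presumably chooses between the t-test and the rank test. Second, a one-sided test needs a direction. For range of motion the hypotheses in 8-3 supply one. For WBC and neutrophils no direction is stated, so it would have to be chosen after the protocol was written.

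Because the rule confirms safety on a non-significant result, a test that ignores one tail makes confirmation easier. A difference in that tail, however large, counts towards safety.

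**Working it through.** **Inputs from the protocol.** 86 evaluable per arm, one-sided alpha 0.025, SD 10, margin 10, difference 15, stated power 0.90323 (8-3 table). No laboratory effect size, SD or alpha is given, and no number of subjects with a day-7 sample.

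**Assumptions.** A standardised difference d = 0.5 SD in WBC or neutrophils. One-sided level 0.025 or 0.05. For 16-1, a two-sided t-test at 0.05. Per-arm n of 86 (everyone evaluable is sampled), 20 or 10 (only those with signs); 20 and 10 are illustrative.

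**Formula.** With n per arm, df = 2n − 2 and noncentrality δ = d·√(n/2). Power is the noncentral-t probability beyond the critical value c.

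**Reproducing the plan's figure.** (15 − 10)/10 = 0.5 SD, n = 86, df = 170, δ = 0.5·√43 = 3.279, c = 1.974. Power = 0.9032, matching 0.90323.

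**Difference of 0.5 SD in the untested direction**

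| n per arm | df | δ (absolute) | c (upper 2.5%) | one-sided 0.025 | one-sided 0.05 | two-sided 0.05 |
|---|---|---|---|---|---|---|
| 86 | 170 | 3.279 | 1.974 | <0.0001 | <0.0001 | 0.903 |
| 20 | 38 | 1.581 | 2.024 | 0.0002 | 0.0007 | 0.338 |
| 10 | 18 | 1.118 | 2.101 | 0.0013 | 0.0032 | 0.185 |

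**Difference of 0.5 SD in the tested direction, 86 per arm**

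| Test | Power |
|---|---|
| one-sided 0.025 | 0.903 |
| two-sided 0.05 | 0.903 |
| one-sided 0.05 | 0.948 |

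One-sided 0.025 and two-sided 0.05 share the critical value 1.974, so here they give the same verdict. At a one-sided level of 0.05 the critical value falls to about 1.65, and a statistic between about 1.65 and 1.97 is significant under 15-2 only.

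**t-test against rank test.** Simulation with lognormal data, 86 per arm, 4,000 runs, comparing the one-sided t-test at 0.025 with the two-sided Wilcoxon at 0.05:

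| Log-scale SD | Log-scale shift | Verdicts differ | of which one- v two-sided t alone |
|---|---|---|---|
| 0.3 | 0 | 4.0% | 2.5% |
| 0.8 | 0 | 4.4% | 2.1% |
| 0.3 | 0.13 | 8.2% | 0% |
| 0.8 | 0.35 | 17.9% | 0% |

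The last column is the disagreement between the one-sided 0.025 and two-sided 0.05 t-tests on the same data. With a real shift in the tested direction it is zero, so the disagreement there comes from the choice between t-test and rank test and grows with skew.

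**The case against.** Five points on the other side have force.

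1. **Sample size.** 86 per arm is the range-of-motion number. Under footnote 2 to the schedule, day-7 blood is taken only in subjects with signs, so the day-7 comparison may be far smaller. Sections 11-1 (4), 11-3 (5) and the Visit 2 list in 11-4 mention the test without that condition, so the number is uncertain. A reader might take 0% against 90% as the effect on this trial; the documents do not support that. This point stands, and is why a range is given.

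2. **Baseline wording.** Both test sentences refer literally to baseline data, and the day-7 sentence in 15-2 names no test. That the one-sided t-test governs the safety rule is an inference from the Visit 1 and Visit 2 criterion and from 15-3 (1). It stands as a limit, but a literal reading is no better: preoperative values cannot show a device effect, and the day-7 comparison would then have no named test.

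3. **Sidedness and alpha.** Section 16-1 does not say two-sided; that is the usual reading of an unqualified t-test in a protocol that writes one side elsewhere. A reader might infer that any statistic between 1.65 and 1.97 flips the verdict. That needs a one-sided level of 5%, which is nowhere stated. The chance of landing there, Φ(1.97 − 1.8) − Φ(1.65 − 1.8) = 0.127 for an expected statistic of 1.8, is also close to its maximum, because 1.8 is almost the midpoint of the band (1.81). With one-sided 0.025 against two-sided 0.05 the band vanishes.

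4. **Direction.** Section 12-4 lists a rise in WBC under infection, and footnote 2 says the day-7 test looks for an increase. A reader might infer that infection-type rises would go unseen. That requires testing against this stated purpose, and the documents do not say so. The likelier unseen difference is a fall, but the direction is not fixed.

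5. **The list in 15-3 (1).** It is not exhaustive, since 15-3 (6) uses Wilcoxon for demographic data. Its omission of Wilcoxon is therefore weak evidence that 15-2 prevails.

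None of this removes the conflict between 15-2 and 16-1.

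**Conclusion.** The conflict is certain: two near-identical paragraphs end in different tests, with no order of precedence. The Wilcoxon option in 16-1 contradicts 15-2 on any reading of sidedness. It is also certain that 15-2 leaves its one-sided test without a stated direction and its normality check without effect.

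The consequence is conditional. If the one-sided test feeds the safety rule, a difference in the untested tail has essentially no chance of being registered. A two-sided 5% test would find an assumed 0.5 SD difference with probability 0.90 at 86 per arm, 0.34 at 20 and 0.19 at 10. In the tested direction nothing changes between one-sided 0.025 and two-sided 0.05 t-tests; against that two-sided test, a gap opens if the one-sided level is 5%. Skewed data can also separate the sections, in 8% to 18% of simulated trials with a true shift at 86 per arm.

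This is a point to correct in a secondary safety comparison. It does not touch the primary analysis or the sample size, and it does not show that a harm signal would be missed. Treating a non-significant difference as confirmation of safety is a separate weakness, which aligning the tests leaves in place.

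**What to change.** Put one specification in 15-2 (2), 15-3 (1) and 16-1 (2), and remove the one-sided restriction from the laboratory analysis:

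- compare WBC and neutrophils between arms two-sided, at a stated alpha, with a 95% interval for the difference;
- use the t-test, or the Wilcoxon rank-sum test when the normality check fails, so that the check has a consequence;
- state that this applies to day-7 as well as preoperative values, and report the number of subjects per arm with a day-7 result.

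The cost is protocol wording: no new data and no change in sample size. The one statistical price is slightly less sensitivity in the single favoured direction if the one-sided level was meant to be 5% (0.948 to 0.903 for 0.5 SD at 86 per arm). If it was meant to be 0.025 and the two-sided alpha is set at 0.05, nothing is lost with the t-test.
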